### Outcomes {12}

The primary outcome will be change in mobility status at the conclusion of the intervention (hospital discharge or the 10th day of the intervention, whichever comes first) compared to the baseline assessment. Mobility status will be assessed at both time points using the Short Physical Performance Battery (SPPB), [42–44] a mobility performance assessment that can be administered in <10 min. It tests gait speed, repeated chair stands, and tandem balance, providing a gross assessment of functional balance, speed, and lower extremity power. It is safe and reliable for use with hospitalized older adults [45] and appropriately sensitive to mobility differences in that population [45, 46]. Further, the SPPB has demonstrated the ability to predict adverse health outcomes including in-hospital falls, [47] post-acute facility placement, [42] subsequent disability, [48] multi-morbidity, [42, 43, 49] and all-cause mortality [42, 50].

We will collect secondary outcomes at the time of hospital discharge including discharge disposition, length of stay, and the presence of hospital-acquired complications (falls, venous thromboembolism, pressure ulcers, and hospital-acquired pneumonia). Additional secondary outcomes will be assessed after hospital discharge and compared to baseline measurement of the same assessments: FRAIL scale score, [51, 52] the patient’s self-rated mobility status according to the AM-PAC mobility outpatient short form (compared to baseline AM-PAC 6-Clicks mobility scores using the AM-PAC T-scale), [53, 54] and the patient’s self-rated participation in activities of daily living using both the Index in Activities of Daily Living (Katz ADL) [55] and the Lawton Instrumental Activities of Daily Living Scale [56]. At this post-hospital time point, we will also assess 30-day hospital readmission and scores on the Patient Reported Outcomes Measurement Information System (PROMIS) physical function subscale [57, 58].

As both a secondary outcome and a method for characterizing the in-hospital mobility of both groups, we will use a medical grade accelerometer to measure steps taken, energy expenditure, activity bouts, sedentary bouts, body position, sleep latency, total sleep time, wake after sleep onset, and sleep efficiency. A random subset of 10–20% of patients discharged to home will continue to wear the device for an additional 10 days so that we can assess changes in activity immediately after discharge.

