### Participant timeline {13}

The baseline assessment and randomization (T0) will occur for each patient within 48 h of hospital admission. They will be enrolled in the study until hospital discharge or after 10 days (T1), whichever occurs first. A post-discharge follow-up call from a study coordinator will be completed 30 days after enrollment (T2). This ensures that the time between T0 and T2 will be 30 days for every patient. The participant timeline, including assessments, is shown in Fig. 2.

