#### Secondary hospital clinical outcomes

Patients’ hospital discharge disposition, length of stay, and the presence of hospital-acquired complications (falls, venous thromboembolism, pressure ulcers, and hospital-acquired pneumonia) will be assessed retrospectively using medical record data, using a unique encounter number to identify study episodes. This number will also be matched to episode-level billing data to identify the cost of the hospital stay.

To characterize the mobility of both randomized groups, each patient will wear a medical grade accelerometer to directly record all movement throughout their hospital stay. The MT will place the accelerometer on the patient’s wrist like a watch (for better compliance and more accurate sleep measurement) with a sampling frequency of 90 Hz and an LFE filter. The device is highly water resistant and does not need to be removed for bathing. It will not display any information to the patient and the patient need not take any action. Raw acceleration data will be translated via algorithms into meaningful activities, including steps taken, energy expenditure, activity bouts, sedentary bouts, body position, sleep latency, total sleep time, wake after sleep onset, and sleep efficiency. Data will be downloaded from each device by the MT at least weekly and at discharge. Except for the random subset of 10–20% of patients who will continue to wear the device at home for an additional 10 days after discharging home, devices will be collected at discharge.

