### Methods for additional analyses (e.g., subgroup analyses) {20b}

We will conduct three sensitivity analyses to account for (1) missing outcomes data, (2) treatment heterogeneity by site, and (3) the dose-response curve in the intervention group.

To identify the patients most likely to benefit from ambulating with a MT, we will build models separately for each treatment arm to predict the outcome of at least 1-point increase in the SPPB (i.e., beyond the minimal clinically important difference). Using the predicted probabilities resulting from these models, we will develop a Classification and Regression Tree (CART) that should identify subsets of patients likely to benefit, not benefit, or be harmed by the treatment. For example, the analysis might show that female patients aged >75 years who have an initial 6-Clicks score between 16 and 18 have an estimated treatment benefit of being 22% more likely to achieve the 1-point increase in SPPB. Essentially the tree will form risk groups of patients with shared characteristics that should receive a similar care recommendation.

We will estimate the total cost of the episode of care including the index admission (from hospital cost accounting systems) and all non-medication costs for the 30 days following enrollment (from Medicare claims) for all patients. For the intervention group, we will add the personnel costs for the MTs (hourly wages plus benefits). Since cost data are skewed, our cost estimates will be transformed and then compared between groups using the *t*-test.

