Our study will be the largest randomized controlled trial to test any exercise intervention for inpatients and tests a simple intervention (walking up to three times per day with a MT) that would be feasible for most hospitals to implement. There will be adequate statistical power to not only detect important differences in the primary outcome of mobility status, but also in less common hospital complications (falls, venous thromboembolism, pressure ulcers, and hospital-acquired pneumonia) that have been suspected to be due, at least in part, to unnecessary bed rest. We will also be able to develop a clinically useful classification model, allowing hospitals to recognize for whom ambulation with a MT may be most beneficial. This classification model will be strengthened by specific data on mobility dosing that we will collect from accelerometers. Lastly, our data will provide clear estimates of intervention costs relative to potential cost savings, information that will be important to help hospitals decide if implementation of a similar program is feasible for them.

Our study has limitations. First, the analyses of dose effect are observational and subject to confounding, as is the heterogeneity of treatment effect analysis to determine which patients benefit most. The cost analyses will suffer from some missing data. We may also have missing data for our primary outcome if patients go home without our knowing. Also, it is not clear whether the AM-PAC mobility measures can be reliably assessed by patient versus clinician raters at different time points without introducing measurement error [26, 75, 76].

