Many potential limitations for our study are mitigated by the study’s design. For example, patients who are enrolled may be unable or unwilling to ambulate three times each day. If adherence is lower than expected in interim analyses, we will compare adherence rates across sites and attempt to identify and spread best practices. If that is not successful, we would still likely have sufficient power to detect a difference in our primary (>99% power with 70% adherence) and secondary outcomes (80% power with 70% adherence). Depending on the ease of enrollment, we may decide to enroll additional patients with the same resources. We anticipate heterogeneous patients, sites, and controls. Given our large sample, we anticipate that all of these important covariates will be balanced between the intervention and control arms. If we find that they are not, we will adjust our outcomes for important confounders. If we are unable to directly identify subgroups for whom the intervention is most beneficial, we will create a score, based on logistic regression, to identify patients who benefit if they score above a certain threshold. Alternatively, we will provide recommendations and tools to enable individual hospitals to incorporate our prediction model into the electronic health record and identify patients directly from the model.

While functional decline in the hospital is multifactorial, general out-of-bed mobility is a modifiable factor for many patients. This randomized controlled trial will test the effectiveness of MT-assisted ambulation on outcomes that matter to both patients and hospitals, including functional status, hospital discharge disposition, and the incidence of potentially avoidable hospital complications. It will also provide a useful estimation of cost implications to help hospital administrators assess the feasibility and utility of creating MT positions in their own hospitals.

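### The Discussion says accelerometer dose will strengthen the who-benefits model; if dose enters as a predictor, the benefit estimate conditions on something that treatment changes

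*Protocol article*

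**What the plan says.** Finding out who benefits is the second of the three primary aims (Objectives {7}). The method is in the section on additional analyses {20b}: "we will build models separately for each treatment arm to predict the outcome of at least 1-point increase in the SPPB". A classification tree is then grown from the predicted probabilities. No predictor list is given. The one worked example uses sex, age and starting function: "female patients aged >75 years who have an initial 6-Clicks score between 16 and 18". The same section lists dose-response, within the treated arm, as a separate sensitivity analysis.

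The Discussion describes the model as "allowing hospitals to recognize for whom ambulation with a MT may be most beneficial" and then adds: "This classification model will be strengthened by specific data on mobility dosing that we will collect from accelerometers". Later, among the fallback options, it offers to let hospitals "incorporate our prediction model into the electronic health record and identify patients directly from the model".

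On timing, Participant timeline {13} says: "The baseline assessment and randomization (T0) will occur for each patient within 48 h of hospital admission". On measurement, the section on secondary hospital outcomes says that "each patient will wear a medical grade accelerometer to directly record all movement throughout their hospital stay". No wear period before randomisation is described. Outcomes {12} introduces the accelerometer data with the words "As both a secondary outcome and a method for characterizing the in-hospital mobility of both groups".

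**The concern.** Accelerometer dose is a consequence of allocation. It is recorded after T0, it is itself a secondary outcome, and raising it is how the intervention is meant to work. The benefit estimate is a contrast between two arm-specific predictions. If dose is among the predictors, that contrast compares treated and control patients who walked the same amount, and three things follow.

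- Any benefit that acts through walking is held fixed and drops out.
- Patients at the same step count are not alike. A control patient who reaches 900 steps unaided is probably fitter than one who reaches it with a MT, so randomisation no longer protects the comparison.
- The model asks for an in-stay step count, which a hospital does not have when it decides whom to assign to a MT.

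At stake is the second aim: the tree could miss, or misplace, the patients for whom the programme works.

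**Working it through.** The plan gives no figure on this point to reproduce. The check has three parts.

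**1. The texts side by side.** The methods section names no accelerometer variable as a predictor, uses baseline traits in its example, and places dose-response elsewhere. The Discussion sentence has the classification model as its subject and says dose data will strengthen it. The two do not match, and only the Discussion links dose to the model.

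**2. Does treatment change dose?** The pilot figures in the Discussion are 668 against 994 steps per day (difference 326, ratio 994/668 = 1.49), with 19% against 28% reaching 900. Fit a lognormal to each arm, with log-mean = ln(mean) - s²/2 and (ln 900 - log-mean)/s = z.

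- Control, z = 0.878: s = 1.296, log-mean = 6.504 - 0.839 = 5.665. Check: (6.802 - 5.665)/1.296 = 0.878.
- Treated, z = 0.583: s = 1.317, log-mean = 6.035.
- Shift on the log scale: 6.035 - 5.665 = 0.370.

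**3. What conditioning on dose does.** From the Sample size section: effect 0.54 SPPB points, SD 2.7. Assumed, because the documents give no values: the share m of the effect that runs through steps (0, 0.5, 1), and an unmeasured illness factor with correlation 0.5 with log-steps and an effect g of 0 or 1 SPPB point per SD.

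On a linear scale, the benefit left when dose is held equal is 0.54(1 - m) - g × 0.5 × 0.37/1.30. For g = 1 the second term is 0.142.

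The protocol's approach was then simulated with 400,000 patients: one logistic model per arm for a gain of one SPPB point or more, with benefit taken as the difference in predicted probabilities. One version used the baseline 6-Clicks score only. The other added log-steps and its square. The last three columns are in percentage points.

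| m | g | Linear benefit left (SPPB points) | True benefit | Baseline predictors only | Dose added |
|---|---|---|---|---|---|
| 0 | 0 | 0.54 | 8.0 | 8.0 | 8.0 |
| 0 | 1 | 0.54 - 0.142 = 0.398 | 8.2 | 8.2 | 6.1 |
| 0.5 | 0 | 0.27 | 7.7 | 7.7 | 3.7 |
| 0.5 | 1 | 0.27 - 0.142 = 0.128 | 8.0 | 8.0 | 1.9 |
| 1 | 0 | 0 | 7.9 | 7.9 | 0.1 |
| 1 | 1 | -0.142 | 8.1 | 8.1 | -1.9 |

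The formula and the simulation agree. In the second row, for example, 0.398/0.54 = 0.74, and 0.74 × 8.2 = 6.1.

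Subgroups were checked with m = 1 and g = 0, assuming that patients with 6-Clicks 16-17 gain more steps (log shift 0.70) than those with 18-20 (0.15). The true benefits were 14.9 and 3.4 points. Baseline predictors returned 14.9 and 3.4. With dose added, the estimates were -0.1 and 0.0, so the contrast the tree should find disappeared.

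**The case against.** The strongest reply is that the operative text never makes dose a predictor. The methods section gives a baseline-only example and keeps dose-response apart, and the limitations treat the dose analysis and the heterogeneity analysis as two things. One line of Discussion prose could mean only that dose data will help interpret the subgroups, for instance by showing whether those who benefited walked more. A predictor list is also commonly left to an analysis plan, which is not shown. This stands as far as it goes: a reader might infer that the protocol has committed to splitting the tree on step counts, and the documents do not establish that. It does not remove the point, because the sentence states an intention about this model, and its plain reading is the harmful one.

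The limitations already concede that the dose and heterogeneity analyses are open to confounding. They do not say that dose is affected by treatment, or that it is missing when patients are selected.

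A reader might also take use in the electronic health record at admission as the model's settled purpose. It is offered only as an alternative among fallbacks, and the text does not mention admission. The availability problem rests instead on the stated aim of helping hospitals recognise who would benefit.

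Finally, it is tempting to quote one expected loss. Suppose a fitness factor correlates 0.7 with steps and adds 0.12 to response probability per SD, and the pilot shift is 0.878 - 0.583 = 0.295 SD. The bias is then 0.12 × 0.7 × 0.295 = 0.025, so a true 6 points becomes 3.5. That set-up has no path through steps, so it shows confounding only and not the loss of a mediated effect, and the 0.7 and 0.12 are not in the protocol. It should not be read as a forecast.

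**Conclusion.** The point holds in conditional form. The Discussion and the methods section are out of step on the role of dose. If the Discussion is followed and dose enters the per-arm models or the tree, the benefit estimate conditions on a post-randomisation variable that treatment changes. That dose is measured after randomisation and moved by treatment comes from the documents. The size of the bias does not: against a true benefit of about 8 percentage points, estimates ran from 8.0 to -1.9. Among the cases tried, the average benefit was unbiased only when steps carried none of the effect and shared no unmeasured cause with recovery, and the first condition contradicts the trial's rationale. That the model would need a value not yet available when patients are selected depends on none of these assumptions.

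The primary analysis, sample size, safety monitoring and data collection are unaffected. The second aim is exposed, and the correction is worth making.

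**What to change.** In the section on additional analyses, state that predictors in the per-arm models and the classification tree are limited to variables known at or before randomisation. Reword or delete the Discussion sentence so that it agrees. Keep accelerometer dose for the separate dose-response analysis, labelled as observational, or for describing walking in each subgroup after the subgroups have been formed. The cost is one or two sentences. No data collection, staffing or sample size changes, because the devices are worn in any case.

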## Trial status

Our study team is currently using protocol version 1 (dated April 25, 2023). Recruitment began on May 15, 2023, and is expected to conclude by May 31, 2026.

## Data Availability

The final trial data set will be retained by the study team, with the primary responsibility of its content and sharing lying with the Principal Investigator.

## Abbreviations

ADL: Activities of daily living
AM-PAC: Activity Measure for Post-Acute Care
CART: Classification and Regression Tree
DSMB: Data Safety Monitoring Board
IRB: Institutional Review Board
JH-HLM: Johns Hopkins Highest Level of Mobility
JH-MGC: Johns Hopkins Mobility Goal Calculator
MT: Mobility Technician
NIA: National Institute on Aging
PROMIS: Patient Reported Outcomes Measurement Information System
SPPB: Short Physical Performance Battery
